## 7.9 Qualitative assessments

This is not directly applicable to this study.

## 7.10 Withdrawal criteria

Withdrawal from the study will only occur if the patient or personal legal representative withdraws consent or safety event in the opinion of the investigators.

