### 7.8 Long term follow-up assessments

Patients will be monitored constantly as part of their routine clinical care in the intensive care unit. For the purpose of the study, follow up data will be recorded hourly from the administration of the last dose

of surfactant (24 hours) until 32 hours post first dose, 4 hourly until 48 hours post first dose and then daily until day 28, or until the time that the patient is discharged from hospital if this takes place first. A chest ultrasound will be performed daily until this time.

There is no anticipated risk of losing patients to follow up given that they will be hospitalised. Patients may choose to withdraw from the study when they re-gain the capacity to consent for themselves. In these cases, no additional data will be collected. Data can be collected retrospectively by the research team as intensive care records will remain available.

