## 8.7 Dosage schedules

Sequential vials of 108 mg Alveofact® in 2.2 mL buffer will be administered by nebulizer at 5-minute intervals with observation of vital signs, changes in oxygen saturation, FiO2 and Mean Airway Pressure. After each administration, 2 drops of normal saline will be nebulized, and the next vial administered. After administration of the first dose, dosing of Alveofact® will pause and vital signs and ventilation parameters will be assessed over the next 8 hours. If no grade 3 or grade 4 adverse events attributable to surfactant administration occur, another dose of Alveofact® will be administered and vital signs and ventilation parameters will be assessed over the next 16 hours. Again, if no grade 3 or grade 4 adverse events attributable to surfactant administration occur; a final dose of Alveofact® will be administered.

The dosing schedule for each group is displayed in the table below.

| Group | 0 Hours           | 8 Hours           | 24 Hours          |
|-------|-------------------|-------------------|-------------------|
| 1     | 10 x 108 mg vials | 10 x 108 mg vials | 10 x 108 mg vials |
| 2     | 10 x 108 mg vials | 10 x 108 mg vials | 30 x 108 mg vials |
| 3     | 10 x 108 mg vials | 30 x 108 mg vials | 30 x 108 mg vials |
| 4     | 30 x 108 mg vials | 30 x 108 mg vials | 30 x 108 mg vials |

If a dose time point is missed it should be administered as soon as it is possible. The investigator or delegate will assess the clinical stability of the patient prior to administering the dose or following a time point being missed or treatment being suspended.

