## 8.7 Dosage modifications

In an event when the administration of 30 vials is not practical, doses may drop to 20 or 10 vials, depending on feasibility. In the event clear efficacy is observed in cohort 1, doses may drop below 10 vials or dosing times may be reduced.

Progression and dosing modifications of subsequent cohorts will be decided by teleconference of the trial steering committee. Any safety concerns would be referred to the independent DSMB on completion of dosing of each cohort of 3 patients + 24 hours to enable collection of physiological outcomes.

The DSMB will actively monitor emerging safety and efficacy data to make recommendations about early study closure or the initiation of a larger randomised controlled clinical trial.

The dose administered cannot be modified due to patient / personal legal representative request.

Given the severity of the illness in ventilated Covid-19 patients, safety data will be interpreted with caution and will not be formally compared between active intervention and control groups.

- Dosing will be stopped in individual patients upon persistent deterioration of oxygenation during or after surfactant administration
- Study stopping rules for futility or efficacy are provided in the statistical analysis section.
- The protocol team will review emerging AE/SAE/SADEs data daily. If 3 or more patients develop the same SAE after administration of study drug, the study will be paused pending review by the DSMB. The study may also pause at the discretion of the Principal Investigator if there are a significant number of unexpected AEs/SAEs/SADEs and referred to the DSMB for review.
- The DSMB will formally review the safety data after every three subjects and is available for ad hoc reviews for other safety concerns as noted above.

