### **9.9 The type and duration of the follow-up of participants after adverse reactions.**

Patient's that experience an adverse reaction as a result of trial treatment will be followed up until day 28 or discharge from hospital. If additional follow up is required for safety reasons the investigator will discuss this with the participant and make appropriate arrangements. Adverse events will be recorded and reported for the duration of the patient's participation in the study. Any SUSAR will need to be

reported to the Sponsor irrespective of how long after IMP administration the reaction has occurred until resolved.

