### Efficacy

The goal of this study is to assess the preliminary efficacy and safety of surfactant administration, identify an efficacy signal quickly (if present) to consider initiation of a larger randomised controlled clinical trial, and assess the potential impact of total dose on preliminary efficacy.

The change in PaO2/FiO2 ratio relative to baseline at 24 hours after the last dose of surfactant and the change in Ventilation Index relative to baseline at 24 hours after the last dose of surfactant will be analysed separately. For each endpoint, a test for a total dose-response effect using a model-based multiple contrast test (Bretz et al, 2005) will be performed. Candidate dose-response models will include linear and Emax. The change in PaO2/FiO2 and change in Ventilation Index may be transformed for analysis (e.g., log transformed) to better satisfy normality assumptions of model residuals. The primary analysis will be done on patients with observed data at 24 hours ("completers"), though sensitivity analyses will also be performed if data are missing at 24 hours in an informative manner (e.g., due to death) where a non-parametric approach can accommodate missing data by assigning the worst rank.

The table below shows the power to show a significant dose response under varying assumed true dose response curves when using 12 matched controls.

| CV                                      | Relative change from baseline, on average |                           |                           |                           |                           | Power to show dose response |
|-----------------------------------------|-------------------------------------------|---------------------------|---------------------------|---------------------------|---------------------------|-----------------------------|
|                                         | Control                                   | Cohort 1 (30 total vials) | Cohort 2 (50 total vials) | Cohort 3 (70 total vials) | Cohort 4 (90 total vials) |                             |
| 20%                                     | 0%                                        | 0%                        | 0%                        | 0%                        | 0%                        | 0.05                        |

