|                                         | 0%                                        | 0%                        | 0%                        | 0%                        | 50%                       | 0.49                        |
| Based on 2000 simulations for each row. |                                           |                           |                           |                           |                           |                             |

When the true residual CV is 20%, there is reasonable power to detect a dose response for either endpoint when the true increase is at least 20-30% in two or more cohorts. There is limited power to detect a dose response when the effect is only in the highest cohort. Also, when the true residual CV is larger, the power reduces substantially. To reduce residual variability, the fitted model will also adjust for the baseline  $\text{PaO}_2/\text{FiO}_2$  ratio or Ventilation Index as a proxy measure of baseline severity. Significant dose response model fits can be utilized to estimate doses that provide clinically meaningful results and aid in planning for future studies.

Efficacy data will be continuously reviewed after each cohort to assess whether results are compelling enough to suggest initiation of a larger randomised controlled clinical trial. Interim efficacy data will be analysed using a simple Bayesian adaptive approach. After each cohort completes dosing plus 24 hours of follow-up, the posterior distributions of the mean change in  $\text{PaO}_2/\text{FiO}_2$  ratio and the mean change in Ventilation Index will be determined under an assumed normal distribution with a non-informative prior. The change in  $\text{PaO}_2/\text{FiO}_2$  and change in Ventilation Index and may be transformed for analysis (e.g., log transformed) to better satisfy normality assumptions. Interim efficacy will be declared for the purposes of further trial planning if there is relatively high posterior probability (e.g., > 80%) that EITHER the true mean change in  $\text{PaO}_2/\text{FiO}_2$  OR mean change in Ventilation Index at 24 hours after last administration of surfactant “high” (e.g.,  $\geq 20\%$ ), either for an individual cohort or for all treated patients combined.

The following table shows the probability of observing at least 80% posterior probability that the true improvement is  $\geq 20\%$  on average for each endpoint.

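### Section 7.10 makes an investigator-judged safety event a ground for leaving the study, and nothing then requires the 48-hour co-primary values

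*Protocol*

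**What the plan says.** Section 7.10 (Withdrawal criteria) is one sentence: "Withdrawal from the study will only occur if the patient or personal legal representative withdraws consent or safety event in the opinion of the investigators". It does not distinguish stopping the study drug from leaving the study.

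Stopping the drug is dealt with in section 8.7. Under Dosage schedules, the second and third doses each depend on a condition: "If no grade 3 or grade 4 adverse events attributable to surfactant administration occur". Under Dosage modifications: "Dosing will be stopped in individual patients upon persistent deterioration of oxygenation during or after surfactant administration". Neither rule says that the patient leaves the trial.

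On data afterwards, section 7.8 schedules recording through 48 hours and then daily to Day 28 or discharge. It rules out further data only for patients who regain capacity and choose to withdraw, and then adds: "Data can be collected retrospectively by the research team as intensive care records will remain available". Section 9.9 says that patients with an adverse reaction to trial treatment "will be followed up until day 28 or discharge from hospital".

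The co-primary endpoints (section 3.3.1) are the changes in PaO2/FiO2 ratio and Ventilation Index at 48 hours after study initiation. Section 10 (Efficacy) measures 24 hours after the last dose, nominally 24 + 24 = 48 hours, and states "The primary analysis will be done on patients with observed data at 24 hours". Worst-rank handling is a secondary step: "sensitivity analyses will also be performed if data are missing at 24 hours in an informative manner".

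**The concern.** A safety event is a good reason to stop surfactant. It is a poor reason to stop observing a patient whose consent still stands, particularly when the outcome is a ventilator reading and a blood gas due within 48 hours. Read literally, 7.10 lets an investigator do the second.

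The patients concerned may not be a random subset. The events listed in section 9.2 include rising FiO2 or PEEP and sustained worsening of ventilation variables, which are close to the components of both co-primary endpoints. The trial is open-label, and an event ascribed to surfactant or the nebuliser can occur only in a treated patient. If such a patient is withdrawn before 48 hours and the records are not used, the completers set loses a poor response from the treated side.

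Each treated cohort has three patients, so one loss removes a third of it. The cohort reviews in section 4 rest on the 48-hour values, and the interim rule in section 10 can be met "either for an individual cohort or for all treated patients combined".

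**Working it through.** **1. Does any passage secure the 48-hour values?**

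| Passage | What it gives | What it leaves open |
|---|---|---|
| 7.10 | Study withdrawal for a safety event | No word on later data |
| 8.7 | Stops dosing only | Does not override 7.10 |
| 7.7 and 7.8, schedules | Recording to 48 h | Silent on a patient withdrawn under 7.10 |
| 7.8, retrospective data | Collection allowed | Permissive, not required |
| 9.9 | Follow-up to Day 28 or discharge | Only after a reaction to trial treatment; co-primary values not named |
| 10, Efficacy | Completers; worst rank as sensitivity | Cannot supply an uncollected value |

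None does. Sections 7.10 and 9.9 also sit awkwardly together: one patient could be both withdrawn and followed.

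**2. Inputs for an illustration of size.** Groups of 8 controls and 3 treated patients in each of four cohorts (section 4); total doses of 0, 30, 50, 70 and 90 vials (section 10); CV 20% (section 10). Log-scale SD = √ln(1 + 0.20²) = 0.198. Assumed: normal changes on the log scale, improvement coded as positive, no baseline adjustment, Emax ED50 of 30 vials. An ED50 of 10 or 45 shifts the results by at most 0.2 points.

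**3. Reproducing the plan's figures.**

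*Power table* (12 controls as the table states, one-sided 5%, log scale, ED50 10, CV 20%): 0.90, 0.82, 0.73, 0.70, 0.64, against the stated 0.89, 0.82, 0.75, 0.72, 0.63. Two-sided and raw-scale versions do not match the table, so the test is taken as one-sided on the log scale.

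*Interim table.* With a flat prior, the mean change is distributed as ȳ + t(n−1)·s/√n. Efficacy is declared if P(mean ≥ ln 1.2) > 0.80 in the current cohort or in all treated patients pooled. With looks after 6, 9 and 12:

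| True change | Simulated | Protocol |
|---|---|---|
| 0% | 0.011 / 0.022 / 0.032 | 0.01 / 0.02 / 0.03 |
| 20% | 0.29 / 0.45 / 0.56 | 0.30 / 0.46 / 0.58 |
| 30% | 0.62 / 0.80 / 0.89 | 0.60 / 0.81 / 0.90 |

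**4. Dose-response test, no true effect.** For each shape f (linear, Emax), contrast c_i ∝ n_i(f_i − f̄) and T = Σc_iȳ_i / (s√Σ(c_i²/n_i)). Reject if the larger T exceeds the multivariate-t critical value for the group sizes that remain. Rejection rate, with loss from the treated arm only:

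| Patients lost | Random | From worst six | From worst four | Exactly the worst |
|---|---|---|---|---|
| None | 0.050 | – | – | – |
| One | 0.051 | 0.064 | 0.071 | 0.095 |
| Two | 0.050 | 0.084 | 0.104 | 0.145 |

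If the worst patient of either arm is lost, the rate is 0.051; for the worst two of either arm, 0.053.

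**5. Interim rule, one endpoint, cumulative to 12 treated patients.**

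| Case | True 0% | True 10% |
|---|---|---|
| All observed | 0.032 | 0.189 |
| One lost at random | 0.043 | 0.207 |
| One poor responder lost | 0.054–0.055 | 0.255–0.268 |
| Two lost at random | 0.048 | 0.213 |
| Two poor responders lost | 0.076–0.078 | 0.320–0.350 |

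With one loss and no effect, 4.3 − 3.2 = 1.1 points come from smaller cohorts and about 5.5 − 4.3 = 1.2 points from selection.

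**6. Planned sensitivity analysis.** A one-sided rank-sum test, 12 against 8, with the missing worst patients given the worst rank, rejects 0.038 (one lost) and 0.019 (two lost).

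**The case against.** The strongest reply is that collection is already the default. Recording to 48 hours is scheduled, routine-care results go into the eCRF (Appendix 1, footnote 1), the bar on further data covers only patients who regain capacity and withdraw, and 9.9 keeps patients with a treatment reaction in follow-up. A treated patient whose oxygenation worsens has a route in 8.7 that stops dosing and nothing else. Section 7.10 is worded restrictively and applies to both arms; controls also undergo tracheal sampling and the choline infusion. Several events in 9.2, such as arrhythmia or bronchospasm, need not mark a poor PaO2/FiO2 ratio or Ventilation Index. Values used for dose decisions are fully source-verified (section 12), collection of efficacy data is reported (section 10, Feasibility), failure to collect primary outcome data is a termination criterion, and the DSMB and TSC review each cohort.

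Much of this stands, and it lowers the stakes. It rules out three stronger readings. A reader might infer that the protocol forbids data after an investigator-led withdrawal; it does not. A reader might infer that the trial's error rate is inflated; the documents give no withdrawal rate and do not show that loss would fall only on treated patients. A reader might take the interim figures as the operating characteristics of the full rule; they cover one endpoint and three looks, whereas section 10 allows a declaration on either endpoint after each cohort.

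What the reply does not do is secure the values. The safeguards would reveal a missing 48-hour reading but not supply it. Nor can this be left to the SAP: whether a site keeps following a patient is a conduct rule, and an analysis plan cannot recover data that sites were not told to collect.

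**Conclusion.** The point holds in a limited form and should be fixed. Section 7.10 turns an investigator-judged safety event into a reason to leave the study, is out of step with 8.7 and 9.9, and leaves the 48-hour co-primary values optional for the patients whose values may matter most to a completers analysis.

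The figures in the working are illustrations. They require withdrawal before 48 hours, unused intensive care records, and loss concentrated on treated poor responders. Under those conditions one loss moves the dose-response test from 5% to about 6 to 9%, and the single-endpoint interim rule from about 3% to 5.5%, above the 5% ceiling that section 10 gives for no true improvement. The planned worst-rank analysis stays below 5% and would partly expose the problem.

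The consequences are bounded: this is an exploratory pilot, interim efficacy is declared only for further trial planning, and safety and death reporting are unaffected. Confidence is medium, because how often 7.10 would be used cannot be known from the protocol.

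**What to change.** Replace the safety clause of 7.10 with wording such as:

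*A safety event, as judged by the investigator, leads to stopping surfactant (section 8.7) and, at the investigator's discretion, any other research procedure (tracheal sampling, choline infusion, study bloods). The patient remains in follow-up unless consent is withdrawn. The PaO2/FiO2 ratio and Ventilation Index at 48 hours after study initiation and the Day 28 outcomes are taken from routine intensive care records, and the patient is analysed in the randomised arm and cohort (see section 9.9).*

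The dosing-stop rules and the right to withdraw consent are unchanged. The cost is a few sentences and a little record abstraction, with no new procedure. The listed study blood gases end at 36 hours (section 7.7 and Appendix 1), so the 48-hour PaO2 and PaCO2 already have to come from routine gases. Section 7.7 puts these at 6 to 12 per 24 hours in usual care, and ventilation parameters are recorded routinely.

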## 7.11 Storage and analysis of clinical samples

All samples will be collected into pre-labelled containers supplied in kits for individual patients by the clinical trial team, will be double bagged and transferred in a closed container between the ICU and the processing laboratory.

- a. Baseline samples of lung TA samples will be collected up to 30 minutes before administration of the first dose of surfactant (t=0h). Samples will then be collected up to 15 minutes before the second (t=8h) and third (t=24h) doses of surfactant, at 16 hours and at 48 and 72 hours thereafter if the patient is still intubated. The TA samples will consist of blind suctioning by a cannula introduced through a port into the endotracheal tube. A volume of 20-50 ml saline will be administered, with an estimated recovery of 8-10 ml. This procedure will not interrupt the ventilator circuit and will not result in desaturation. TA samples will be taken into pre-labelled tissue culture (Falcon) tubes and stored at +4°C in the ICU sample fridge until transfer to the laboratory for processing. Transfer to the laboratory should be as rapid as possible, with a goal of under 2 hrs.
- b. Blood samples (10 ml) will be collected into EDTA vacutainers and an additional sample (9) ml will be taken and fixed in Transfix tubes. Samples will be stored at +4°C until transfer to the laboratory for processing.
- c. TA samples will be centrifuged at 400 x g x10 mins and the supernatant removed. Cell pellet differential white cell distributions will use cytopsins after fixation. Aliquots for the different assays will be prepared from the supernatant. The aliquot for lipid analysis (800 µl) will be added to ice-cold methanol in glass vials and stored at -20°C until analysis. One aliquot of supernatant (1.5 ml) will be taken for surfactant protein analysis with the remainder stored in aliquots (1 ml) in cryovials. All cryovial samples will be stored at -80±5°C until analysis.
- d. Blood samples will be centrifuged at 1200 x g x 10 mins. Two aliquots of plasma (200 µl) will be added to glass vials containing ice-cold methanol (2 ml) and stored at -20°C until lipid analysis. The remaining plasma will be stored in aliquots (500 µl) in cryovials at -80±5°C. Blood samples in Transfix tubes will be stored at +4°C.

All samples will be stored within sealed storage containers in identified secure refrigerators and freezers. Temperature of the -80°C freezers will be checked daily by a data logger.

There will be a schedule of courier transfer between the three analytical sites. As Transfix tubes can be stored for up to 7 days before analysis, the 6 samples from each patient will be stored together and sent to Manchester in individual patient batches. Sample transfers between the London and Southampton sites will be scheduled for completion of the trial.

All aliquots of TA and blood plasma samples that remain after the analytical procedures will be stored at  $-80\pm5^{\circ}\text{C}$  until a decision to gift samples for future research is made either by patients after recovery or by a personal legal representative for patients who have died. If such permission is refused, samples concerned will be destroyed according to the normal trust guideline.

Virus will be destroyed where practicable in the samples for analysis. This will be achieved for the lipid analyses during extraction by adding samples to methanol, by UV irradiation for the surfactant protein analysis and by fixation for the inflammatory cell characterisation. All procedures on samples with live virus will be undertaken in category 2 or 3 facilities as appropriate and related SOPs will be supplied. They will be:

1. Blind closed suction TA samples, giving 20-50 ml saline with typical recovery of 8-10 ml
2. EDTA blood samples.

Analyses to be undertaken by laboratories at Southampton, London and Manchester on samples from both surfactant and control groups are:

